### Outcome Measures

The primary outcome measure is the Wolf Motor Function Test (WMFT) (40) after 6 weeks of treatment (end of treatment). The average time to perform 15 functional tasks (maximum, 120 s per task; if >120 s, the score is 121 s) as well as the quality of movement (Functional Ability Scale; range, 0 to 5) are assessed. The Minimal Clinically Important Differences (MCID) in the chronic phase are 1.2 to 2 s for the average time to complete the tasks, and 0.2 to 0.4 points for the Functional Ability Scale (41). The WMFT is a valid instrument with high interrater and test-retest reliabilities, as well as high internal consistency (42). The original version of the WMFT was developed to assess the effects of CIMT in stroke and traumatic brain injury.

The secondary outcomes are the WMFT at 3, 10 and 18 weeks after beginning of treatment, as well as the following outcomes measured at 3, 6, 10, and 18 weeks after beginning of treatment: MAL; active range of motion (ROM) of wrist extension and flexion; grasp and pinch strength in the paretic and non-paretic sides (the order of testing is randomized within and across subjects); MAS; FMA-UL in the paretic arm; BI; SIS; Beck Depression Inventory Short Form. Measurements assessed after 3 and 6 weeks of treatment are scheduled for days other than those in which the patients receive treatment, in order to avoid fatigue.

In addition, ROM of wrist extension and flexion is measured before and after the first session of treatment. ROM of wrist extension and flexion is measured with an analogic goniometer (ISP® Instituto São Paulo, São Paulo, Brazil) (43). Averages of three trials are calculated. Grip strength is measured with a Jamar dynamometer (Saehan Jamar, Changwong Korea) and pinch strength, with a digital dynamometer (Kratos, São Paulo, Brazil) (44). The trunk and the arms are stabilized and the wrist is kept in a neutral position during measurements.

All outcomes are evaluated by trained researchers blinded to the type of RPSS administered to patients. Assessments are videotaped.

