### Sample Size

We planned to include up to 40 patients and to determine the final sample size after evaluating the results of the first twenty patients included in the trial in regard to the MCID of the primary outcome (change in WMFT, Functional Ability Scale at 6 weeks compared to baseline).

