### Data Analysis

Analysis of variance with repeated measures or generalized estimating equations models with factors GROUP (active or sham) and TIME (baseline, 3, 6 weeks) will be performed, according to the distribution of the data. After all follow-ups have been completed, analyses will be performed with factors GROUP (active or sham) and TIME (baseline, 3, 6, 10, and 18 weeks). If there is an imbalance in Fugl-Meyer scores between the groups, then the analysis will be adjusted for baseline severity.

Also, the percentages of patients in the active and sham groups who will attain gains equal or larger than MCID in the WMFT and MAL, FMA-UL at 6, 10, and 18 weeks will be compared with chi-square tests or Fisher's exact tests.

Compliance with the interventions will be compared in the active and sham groups with Mann–Whitney tests.

Intention-to-treat (ITT) and per-protocol analyses will be performed. For intention-to-treat analysis, missing observations will be imputed with the Last Observation Carried Forward (LOCF).

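### As a plain covariate, baseline Fugl-Meyer leaves the GROUP x TIME treatment contrast unchanged; the plan does not state the Fugl-Meyer x TIME term that would adjust it

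*Protocol article*

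**What the plan says.** All of this is in the protocol article.

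- **Data Analysis, first model:** repeated-measures ANOVA or GEE "with factors GROUP (active or sham) and TIME (baseline, 3, 6 weeks) will be performed, according to the distribution of the data". Baseline is therefore part of the response, not a covariate.
- **Data Analysis, after follow-up:** "analyses will be performed with factors GROUP (active or sham) and TIME (baseline, 3, 6, 10, and 18 weeks", with the same structure and five visits.
- **Data Analysis, adjustment:** "If there is an imbalance in Fugl-Meyer scores between the groups, then the analysis will be adjusted for baseline severity". The text does not say whether severity enters as a single term or crossed with TIME.
- **Data Analysis, missing data:** LOCF for the intention-to-treat analysis, which fills every visit.
- **Sample Size:** the "primary outcome (change in WMFT, Functional Ability Scale at 6 weeks compared to baseline" is what the trial is judged on. In a model with baseline as a TIME level, that is the week-6 GROUP x TIME term.
- **Outcome Measures:** FMA-UL is also a secondary outcome ("MAS; FMA-UL in the paretic arm; BI; SIS").

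**The concern.** The Fugl-Meyer sentence is the only stated protection against a chance difference in severity. The trial is small, its entry range is wide (Fugl-Meyer 7 to 50), and allocation is in blocks of four with no stratification by severity mentioned. The most direct way to carry out the sentence is to add baseline Fugl-Meyer as one more term to the GROUP and TIME model. That step does not alter the change-from-baseline contrast. A result labelled as severity-adjusted could then equal the unadjusted one. If more and less impaired patients gain by different amounts, the effect of the imbalance would remain in it.

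This differs from the usual objection to adjustment triggered by observed imbalance. Making the adjustment unconditional in the same model would still leave GROUP x TIME where it was.

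**Working it through.** The plan gives no standard deviation, slope or imbalance threshold, so there is no figure of its own to reproduce. The check is algebra, then simulation, then a range for the size.

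**Inputs from the protocol article:** TIME levels and LOCF (Data Analysis); change to week 6, up to 40 patients and an evaluation after the first twenty (Sample Size); 1:1 allocation in blocks of four, so 20 or 10 per arm (Randomization); Fugl-Meyer 7 to 50 (Table 1); MCID 0.2 to 0.4 on the Functional Ability Scale (Outcome Measures).

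**Assumed, not in the document:** the shape of the Fugl-Meyer distribution, the dependence of gain on severity, and the imbalance used in the simulation.

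**Step 1, algebra.** Let X_i be baseline Fugl-Meyer and G_i the arm (A active, C sham):

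Y_it = mu_t + a·G_i + d_t·G_i + b·X_i + e_it, with d_0 = 0.

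On complete data, GROUP x TIME gives each arm-by-visit cell its own mean, fitted as Ybar_gt − b·Xbar_g. So

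d_6 = [(Ybar_A6 − b·Xbar_A) − (Ybar_A0 − b·Xbar_A)] − [(Ybar_C6 − b·Xbar_C) − (Ybar_C0 − b·Xbar_C)] = (Ybar_A6 − Ybar_A0) − (Ybar_C6 − Ybar_C0).

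The slope b disappears whatever its value. If the slope may differ by visit (b_t·X_i), the estimate becomes this quantity minus (b_6 − b_0)·(Xbar_A − Xbar_C). That last term is the adjustment wanted.

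**Step 2, simulation.** Exchangeable GEE, identity link, 20 per arm, visits 0, 3 and 6, true treatment effect 0. Assumed imbalance 0.8 SD and extra gain 0.3 per SD of severity, so the expected error is 0.8 × 0.3 = 0.24.

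| Model | One dataset: estimate (SE) | 400 replicates: mean | Rejection rate |
|---|---|---|---|
| No severity term | 0.2284 (0.1404) | 0.238 | 45.8% |
| Severity as plain covariate | 0.2284 (0.1404) | 0.238 | 45.8% |
| Severity x TIME | −0.0471 (0.1135) | −0.0015 | 7.3% |

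The largest difference between the first two rows over all replicates was 7e-16, which is rounding error. ANCOVA of week 6 on the outcome's baseline and severity averaged 0.0009.

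**Step 3, where the cancellation is not exact or does not matter.**
- 15% of post-baseline values missing, no imputation: the plain covariate moved the estimate by at most 0.048, and the mean error stayed at about 0.24.
- Log-link gamma GEE, one dataset: the plain covariate moved the interaction from 0.488 to 0.403.
- Gain unrelated to severity, one dataset: 0.169 without severity and with it as a plain covariate, 0.172 with severity x TIME. Nothing needed correcting.
- The GROUP effect averaged over visits did change (0.733 to 0.105), but it mixes in the pre-treatment visit.

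**Step 4, plausible size.** If Fugl-Meyer is uniform on 7 to 50, SD = 43/√12 = 12.41.
- 20 per arm: SE of the arm difference = 12.41 × √(2/20) = 3.93; 1.96 × 3.93 = 7.7 points.
- 10 per arm: 12.41 × √(2/10) = 5.55; 1.96 × 5.55 = 10.9 points.
- At an assumed 0.01 to 0.02 Functional Ability Scale points per Fugl-Meyer point: 7.7 × 0.01 = 0.08 to 7.7 × 0.02 = 0.15 with 40 patients; 10.9 × 0.01 = 0.11 to 10.9 × 0.02 = 0.22 with 20.

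**Step 5, FMA-UL as outcome.** With baseline as a TIME level and FMA-UL x TIME fitted, the baseline response is the covariate itself and its residual is zero. That conflicts with the variance assumptions of repeated-measures ANOVA, so this outcome needs separate treatment.

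**The case against.** The strongest reply is that the article never says severity enters as a plain covariate. Severity x TIME is a usual form of repeated-measures ANCOVA, some software adds it by default, and a condensed article may leave such detail to an analysis plan that is not shown. This stands against the stronger reading a reader might infer, that the planned adjustment cannot reach the treatment comparison and an imbalance must stay uncorrected. The text does not support that reading. What remains is that the article itself fixes baseline as a TIME level. That choice makes the safeguard depend on an unstated term, and a better model is available from data already collected.

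Other points that stand:
- GROUP x TIME is not named as the test. If the arm difference at week 6 were read from the same model instead, a plain covariate would shift it by slope times imbalance. The change definition in Sample Size makes GROUP x TIME the natural reading, not the only one.
- The choice of model by data distribution leaves a non-identity link open, and LOCF is stated only for intention-to-treat. Exact cancellation is limited accordingly.
- The simulated imbalance is deliberately large: 0.8/√(2/20) = 2.5 standard errors. Its slope, 0.3/12.41 = 0.024 per point, exceeds the range in Step 4. The 45.8% rate shows the mechanism and is not an expected error rate. Over all randomisations, the unadjusted standard error already allows for chance imbalance.

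A reader might also infer that the responder comparisons ("at 6, 10, and 18 weeks will be compared with chi-square tests or" Fisher's exact tests) are faulty because they take no covariate. The adjustment sentence follows the repeated-measures models and promises nothing for the responder tests. Unadjusted tests of a secondary comparison are not an error.

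**Conclusion.** The point holds in limited form. With baseline as a TIME level and change to week 6 as the primary outcome, a plain Fugl-Meyer covariate leaves GROUP x TIME unchanged in repeated-measures ANOVA or identity-link GEE on complete or LOCF-completed data. This is exact and needs no assumption about the data values. The change contrast is adjusted only if Fugl-Meyer x TIME is fitted, and the article does not state that it will be.

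The practical size is uncertain. It is zero if severity does not predict gain. Under the assumed uniform distribution and slopes, at the 95% limit of chance imbalance, the error stays below the lowest MCID of 0.2 with 40 patients and just reaches it with 20. The document gives neither the slope nor the distribution. The matter should be settled before unblinding, but it does not show that the trial's result will be biased.

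**What to change.** Preferred: take baseline out of TIME. Model weeks 3 and 6 (later 3, 6, 10 and 18) with GROUP, TIME, GROUP x TIME, the outcome's own baseline x TIME and baseline FMA-UL x TIME. Name the week-6 active-minus-sham contrast as the treatment effect. When FMA-UL is the outcome, its baseline enters once. The covariates are then in the model whatever the observed balance, so no imbalance threshold is needed.

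Alternative, if baseline must stay a TIME level: prespecify FMA-UL x TIME for every outcome except FMA-UL, and use the post-baseline model for FMA-UL.

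Cost: wording only, no new data, and a few degrees of freedom. Precision can move either way. In the single simulated datasets, adding severity x TIME to the model with baseline kept as a TIME level lowered the standard error from 0.140 to 0.113 when severity predicted gain. It raised it from 0.082 to 0.099 when severity did not, under the same large imbalance.

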The proposed protocol will thus provide novel information about the effects of RPSS as an add-on intervention to motor training, under a protocol adapted to a developing-world environment, with shorter duration of treatment sessions, distributed over a longer period of time. Furthermore, the protocol has other differences in comparison to the paradigm applied by previous studies: (11, 46) first, recurrent strokes are included in the present protocol but were excluded by others (11, 46). Recurrent strokes are more common in developing countries such as Brazil compared to developed countries, and represented the most common reason for exclusion (45%) in a prior study of neuromodulation in stroke rehabilitation in Brazil (47). Because this protocol intended to be applied in a developing country, recurrent strokes were not excluded.

Second, while Carrico et al. (11) and Yadav et al. (46) administered RPSS to the Erb's point to provide brachial plexus stimulation, in addition to the median and radial nerves, in the current protocol RPSS is administered to the median, radial and ulnar nerves on the wrist/arm as previously reported (33). RPSS with Erb's point stimulation had not been described when the current protocol was designed, while nerve stimulation on the wrist/arm had been previously shown to be well-tolerated (10).

Follow-ups will continue up to 3 months post-treatment in the current protocol, providing information about long-term duration of effects of RPSS as an add-on intervention to treatment. Also, the evaluation of outcomes at 3 weeks aims to investigate whether 9 sessions of treatment lead to similar effects, compared to 18 sessions of treatment. If this hypothesis is proven correct, larger multicenter studies could be conducted faster, and at lower costs. According to current standards of payment of rehabilitation therapy and interventions of non-invasive peripheral stimulation in public health services in Brazil (http://sigtap.datasus.gov.br/tabela-unificada/app/sec/inicio.jsp), the costs of the entire treatment would be approximately 700 Brazilian reals (or 155 dollars).

Finally, detailed imaging data, including DTI analysis, is used in the proposed protocol in order to characterize the degree of involvement of the corticospinal tract, key to motor recovery after stroke, (48) in both the active and sham groups.

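### LOCF is the only missing-data method in the intention-to-treat analysis; it can bias the week-6 contrast in either direction and imposes persistence on patients last seen at week 6

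*Protocol article*

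**What the plan says.** Under Data Analysis, the protocol article names two analysis sets: "Intention-to-treat (ITT) and per-protocol analyses will be performed". It then fixes the missing-data rule for the intention-to-treat analysis: "missing observations will be imputed with the Last Observation Carried Forward (LOCF"). It states no assumption about why data are missing and no alternative to LOCF.

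The rule applies to these analyses:

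- **Primary endpoint** (Outcome Measures): "The primary outcome measure is the Wolf Motor Function Test (WMFT) (40) after 6 weeks of treatment (end of treatment"). The first model uses "TIME (baseline, 3, 6 weeks) will be performed, according to the distribution of the data", so a missing week-6 value can only be filled from baseline or week 3.
- **Follow-up** (Data Analysis): "analyses will be performed with factors GROUP (active or sham) and TIME (baseline, 3, 6, 10, and 18 weeks"). The Discussion gives the purpose of this follow-up as "providing information about long-term duration of effects of RPSS as an add-on intervention to treatment".
- **Week 3** (Discussion): "the evaluation of outcomes at 3 weeks aims to investigate whether 9 sessions of treatment lead to similar effects, compared to 18 sessions of treatment".
- **Responder tests** (Data Analysis): the proportions reaching the MCID at 6, 10 and 18 weeks.

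**The concern.** LOCF sets a patient's change after the last visit to zero. That conflicts with the design in three places.

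1. **Week 6.** Both arms receive FES, task-specific training and daily home tasks, which are meant to produce improvement. A patient lost early is frozen at no gain (baseline carried) or at the gain after 9 of 18 sessions (week 3 carried). The effect on the contrast depends on how many are lost in each arm and how much change was still to come in each.
2. **Weeks 10 and 18.** A patient last seen at week 6 keeps the end-of-treatment score. Persistence is then assumed for that patient, although persistence is what the follow-up is meant to measure.
3. **9 versus 18 sessions.** A patient last seen at week 3 contributes identical values at weeks 3 and 6, which pushes the comparison toward similarity.

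The filled values also enter the models and responder tables as if they had been observed. At stake are the primary contrast and two aims stated in the Discussion.

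**Working it through.** The protocol gives no alpha, SD, expected gain or dropout rate, so there is no figure of its own to reproduce.

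**Inputs from the document.** Up to 40 patients randomised 1:1, so 20 per arm. MCID for the Functional Ability Scale 0.2 to 0.4 points. Visits at baseline and weeks 3, 6, 10 and 18.

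**Assumed inputs.** Gains, dropout rates, SD of change 0.3 to 0.5, two-sided 5% t-test on week-6 change, and dropout completely at random within arm.

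**Formula.** With loss d and mean gain g in the active (A) and sham (S) arms, the expected LOCF contrast at time t is

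[(1 - dA) x gA(t) + dA x gA(last)] - [(1 - dS) x gS(t) + dS x gS(last)]

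**1. Week 6, no true difference** (gain 0.4 in both arms, all loss before week 3, so gain carried = 0).

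- 20% / 10% loss: 0.80 x 0.4 - 0.90 x 0.4 = 0.32 - 0.36 = **-0.04**, or 20% of the lower MCID bound. Simulated type I error (40,000 runs): 6.0% to 6.9%.
- 25% / 5% loss: 0.75 x 0.4 - 0.95 x 0.4 = 0.30 - 0.38 = **-0.08**, or 40% of that bound. Type I error: 8.5% (SD 0.5) to 13.1% (SD 0.3).
- 20% / 10% loss, half of it after week 3 (week-3 gain 0.2): (0.32 + 0.10 x 0.2) - (0.36 + 0.05 x 0.2) = 0.34 - 0.37 = -0.03. Type I error: 5.5% to 6.1%.
- 10% / 10% loss: no bias and no inflation.

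Swapping the arms reverses the sign.

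**2. Week 6, true difference 0.40** (gains 0.6 and 0.2, baseline carried).

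| Loss A / S | Calculation | LOCF contrast |
|---|---|---|
| 20% / 20% | 0.8 x 0.6 - 0.8 x 0.2 | 0.32 |
| 30% / 10% | 0.7 x 0.6 - 0.9 x 0.2 | 0.24 |
| 10% / 30% | 0.9 x 0.6 - 0.7 x 0.2 | 0.40 |

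If week 3 is carried instead (gains 0.3 and 0.1), 20% / 20% gives (0.48 + 0.06) - (0.16 + 0.02) = 0.36. Unequal loss is therefore not sufficient for bias (third row), and it is not necessary either (first row).

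**3. Week 18, patients last seen at week 6.** Suppose the active gain falls from 0.6 to 0.2 and the sham gain stays at 0.2. The true week-18 difference is 0.

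- 20% / 20%: (0.8 x 0.2 + 0.2 x 0.6) - 0.2 = 0.28 - 0.20 = **0.08**
- 10% / 10%: 0.1 x (0.6 - 0.2) = 0.04
- 30% / 10%: (0.7 x 0.2 + 0.3 x 0.6) - 0.2 = 0.32 - 0.20 = 0.12

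If both arms instead lose 0.2 (0.6 to 0.4, and 0.2 to 0.0), 20% / 20% gives (0.32 + 0.12) - (0 + 0.04) = 0.40. That equals the true difference, so the contrast is not biased.

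**4. 9 versus 18 sessions.** With an active gain of 0.3 at week 3 and 0.6 at week 6, the true further gain is 0.3. If 20% were last seen at week 3, LOCF reports 0.8 x 0.3 = 0.24.

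**5. Filled values treated as observed.** At 20% loss, 0.20 x 20 = 4 values per arm are filled and counted as data. With equal loss and no true effect, simulated type I error stayed near 5%, so in these scenarios the inflation comes from the bias in the mean.

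**The case against.** **A reader might infer that LOCF biases week 6 whenever loss differs by arm.** Working step 2 shows otherwise: 10% / 30% loss returns exactly 0.40, and equal loss can still bias. What matters is the combination of loss and change still to come.

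**A reader might infer that LOCF always makes effects look lasting.** The documents do not support this. Only patients last seen at or near week 6 keep an end-of-treatment score. Those lost before week 3 carry baseline to weeks 10 and 18, which pulls toward no effect. Fading is itself an assumption: the home tasks and the signed contract to use the paretic limb (Motor Training) might sustain gains, and LOCF would then understate them. Equal decay with equal loss leaves the contrast unbiased.

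**A reader might take 13% as the likely type I error.** It needs a five-fold imbalance in loss, all before week 3. Nothing in the protocol points to that. Both arms have 90 minutes of stimulation and the same training, missed sessions trigger a call, and transport is paid. At 20% / 10% the figure is about 5.5% to 7%.

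The study is also described as preliminary, and with no dropout LOCF does no harm. These points limit the size and the severity of the problem but do not remove it. LOCF is a stated choice, so it cannot be put down to condensation in an article or deferral to an SAP. The per-protocol analysis does not test the missing-data assumption. Some loss is foreseeable with 18 three-hour sessions, 18 weeks of follow-up and the dependence on caregivers that the Discussion raises. Nor is LOCF reliably conservative, because its direction is not fixed.

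**Conclusion.** The concern holds in limited form: should-fix. The single missing-data rule assumes no change during a treatment phase designed to produce change, and again during a follow-up designed to detect change.

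Under the assumed inputs, the week-6 error in the no-effect case is 0.04 for moderate imbalance and 0.08 in the worst case examined. With a true difference of 0.40, equal 20% early loss takes away 0.08. A fully faded effect is reported as 0.08 at week 18 when 20% per arm were last seen at week 6. Each 0.08 is 40% of the lower MCID bound of 0.2.

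All these sizes scale with the missing fraction, which the protocol does not give. The direction at week 6 cannot be predicted in advance. The durability bias in the contrast requires that the between-arm effect fades, or that loss after week 6 is unequal while gains decay.

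**What to change.** Before unblinded analysis, replace LOCF as the main intention-to-treat method with one that is valid under missing at random and keeps all randomised patients. Either of these would do:

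- **Multiple imputation by arm**, from baseline and all observed visits, feeding the planned ANOVA or GEE and the MCID responder tests. This leaves the planned choice of model by data distribution intact, which matters because WMFT time is capped at 121 s and the ability scale is bounded at 0 and 5.
- **A likelihood-based mixed model with baseline as a response**, constrained equal across arms. Entering baseline only as a covariate would not be enough: patients lost before week 3 have no post-baseline value and would drop out of the analysis. The responder tests would still need imputation.

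Unweighted GEE on observed data alone is not a substitute, because it generally needs data missing completely at random. State the missing-at-random assumption, add a sensitivity analysis for departures from it, and keep LOCF only as a labelled sensitivity analysis.

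The cost is a change of analysis wording and use of standard software, with no new visits or data. The downsides are a somewhat wider interval, reliance on missing at random, and the need for a sparse imputation model with about 20 patients per arm.
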